### Methods in analysis to handle protocol non-adherence and any statistical methods to handle missing data {20c}

Missing data will be replaced by multiple imputed values.

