**Methods:**

This multicenter randomized crossover study will be conducted in three phases and will involve 120 dyslexic children between the ages of 8 and 13 years. The first phase serves as within-subject baseline period that lasts for 2 months. In this phase, all children undergo weekly speech-language therapy sessions without additional training at home (business-as-usual). During the second phase, all dyslexics receive three types of intensive interventions that last 2 month each: Phonological, visual-attentional, and cross-modal. The order of the first two interventions (phonological and visual-attentional) is swapped in two randomly assigned groups of 60 dyslexics each. This allows one to test the efficacy and additivity of each intervention (against baseline) and find out whether the order of delivery matters. During the third phase, the follow-up period, the intensive interventions are stopped, and all dyslexics will be tested after 2 months. Implementation fidelity will be assessed from the user data of the computerized intervention program and an “intention-to-treat” analysis will be performed on the children who quit the trial before the end.

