#### Exclusion criteria (or study exit criteria)

Participants are temporarily or permanently excluded from the study if:They interrupt daily training for more than a continuous period of 15 days without a valid reason determined at the investigator’s discretion.They do not participate regularly in daily training, as left to the investigator’s appreciation.The participants or their parents withdraw their consent.

The interruption may occur after consent has been obtained or after randomization. A child who wishes to withdraw consent may tell his/her parents or the speech-language pathologist who will inform the principal investigator. Parents may also inform the principal investigator directly (contact information is available at the end of the information sheet that goes with the consent form). For, all patients, the speech-language pathologist must send a patient identification form to the principal investigator indicating the date the consent was signed, the date of randomization, the randomization group, and, if applicable, the date of discharge from the trial.

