### Criteria for discontinuing or modifying allocated interventions {11b}

The criteria for discontinuing or modifying allocated interventions are: (a) a serious adverse event (disease or pandemic) or environmental event (relocation), (b) withdrawal of consent, (c) cessation of daily training for more than 15 days without valid reason and subject to the judgment of the investigator, or an irregularity in daily training subject to the judgment of the investigator. Post-intervention measures for children that drop out from the intervention will be taken to perform an intention-to-treat analysis.

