### Sample size {14}

In a pilot study on 20 patients with dyslexia, we determined that the effect size on reading efficiency between classical rehabilitation (baseline) and intensive rehabilitation was Cohen d = 0.867. Given that the literature on interventions for children and adolescents with reading disabilities gives effect sizes of 0.322 for phonological interventions (see [34]), expected effects on reading skills of a multimodal phonological, visual-attentional and cross-modal intervention should be greater. However, we preferred to be conservative and reduced the expected effect size to Cohen’s d = 0.700. Using G*Power 3.1.9.6, we found *n* = 55 per group. With an estimated drop-out rate of 10%, we will therefore include 120 participants.

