### Plans to promote participant retention and complete follow-up {18b}

The principles of therapeutic education and shared decision making are used to maintain the children’s participation during the 16 months. Participants and their parents receive all the information necessary to understand developmental dyslexia and the protocol of care offered to them. This information is presented and repeated throughout the duration of the study on different media (slide show and fact sheets). Most interventions at home are standardized and computerized. The role of the parents is making sure that the children respect the daily sessions, supporting them by being present during the numerical training and carrying out the verbal trainings such as BlendSeg or ARMAR. The children and their parents are also trained in using the software on their own by means of tutorials. The outcomes obtained during the different phases of the study are communicated very precisely and explained to the parents and children. The child can decide to leave the study at any time. The data collected until the withdrawal of consent or the end of participation is kept and analyzed as specified in the information leaflet given to the parents.

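### One multiple-imputation rule covers every missing score, so children who stop training and are not measured afterwards could be credited with trained children's gains

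*Protocol article*

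**What the plan says.** Item 20c of the protocol article has a heading that covers both protocol non-adherence and missing data. Its whole content is one sentence: "Missing data will be replaced by multiple imputed values". It does not distinguish reasons for missingness.

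Other sections determine which scores will be missing, and they differ:

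- **Exit criteria.** "Participants are temporarily or permanently excluded from the study if" introduces a list that includes interrupting daily training for more than 15 continuous days and training irregularly. These children leave the *study*, and a discharge date is recorded on the identification form.
- **Item 11b.** Nearly the same trigger, "cessation of daily training for more than 15 days without valid reason and subject to the judgment of the investigator", is listed as a reason for discontinuing or modifying the *intervention*. The item then says: "Post-intervention measures for children that drop out from the intervention will be taken to perform an intention-to-treat analysis".
- **Item 18b.** "The data collected until the withdrawal of consent or the end of participation is kept and analyzed". Nothing is said there about measurement after that point.
- **Abstract, Methods.** An intention-to-treat "analysis will be performed on the children who quit the trial before the end".

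Under the Statistical analysis heading, the main comparison sets each child's gains in the training phase against the same child's T1–T2 gain under weekly therapy alone. Under Trial design, all children receive all three interventions, and there is no untrained control group.

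**The concern.** An intention-to-treat estimate should reflect what happened to all children, including those who stopped training. Item 11b supports this by planning to measure them. The exit criteria and item 18b can be read as ending data collection at exit, and the trigger for exit is not training. Where that reading is followed, missing later scores belong disproportionately to children who were off training.

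An imputation model that ignores training status learns the later gains mainly from children who kept training and assigns them to children who did not. In a parallel trial with an untrained arm and similar drop-out, part of such an error could offset between arms. Here every child is trained and the main contrast is within-child, so the error passes directly into the main estimate. That estimate then drifts towards the effect had everyone kept training, which is not what the abstract and item 11b promise.

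**Working it through.** **Inputs from the protocol article**

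- Effect size, Sample size section: "we preferred to be conservative and reduced the expected effect size to Cohen’s d = 0.700".
- Drop-out 10%, 120 children in total (same section).
- Significance threshold 5% (Statistical methods, item 20a).

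**The plan's own figure.** The article reports 55 per group ("Using G*Power 3.1.9.6, we found" introduces it) without stating power or sidedness. An exact two-sample t-test at d = 0.70, two-sided 5%, needs 34, 44 and 55 per group for 80%, 90% and 95% power. The stated 55 therefore matches 95% (achieved 95.3%). Allowing for drop-out, 110 / 0.9 = 122.2, so 123; the planned 120 is within 3% of that. The planning inputs are coherent and are used below. I treat 0.70 as the standardised excess of the training-phase gain over the T1–T2 gain. This is a simplification, because the article lists several separate gain contrasts.

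**Assumed quantities, not in the documents**

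- q = share who stop training (10% taken from the drop-out figure)
- r = share of the training gain that quitters keep
- u = share of quitters with no later measurement

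**Formulas**

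- Effect in all children: 0.70 × [(1 − q) + q·r]
- Estimate when unmeasured quitters are imputed at the trained children's gain: 0.70 × [(1 − q) + q(1 − u)r + q·u]
- Overstatement, by subtraction: 0.70 × q × u × (1 − r)

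**Results at q = 0.10**

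| Gain kept (r) | Unmeasured (u) | Effect in all children | Imputed estimate | Overstatement |
|---|---|---|---|---|
| 0 | 1 | 0.70 × 0.90 = 0.630 | 0.700 | 0.070 (11.1%) |
| 0 | 0.5 | 0.630 | 0.665 | 0.035 (5.6%) |
| 0 | 0 | 0.630 | 0.630 | 0 |
| 0.5 | 1 | 0.70 × 0.95 = 0.665 | 0.700 | 0.035 (5.3%) |
| 1 | any | 0.700 | 0.700 | 0 |

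In the second row the formula runs slightly high, because measured quitters also enter the imputation pool: 0.63 / 0.95 = 0.663, an overstatement of 0.033.

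**Check by simulation.** The set-up was 120 children, each with a 10% chance of quitting, quitters keeping no gain, SD 1 for the difference in gains, 20 imputations and 3000 runs. The case with an off-training indicator used only runs with at least two measured quitters.

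| Case | Mean estimate | SD of estimates |
|---|---|---|
| All quitters measured | 0.632 | 0.094 |
| None measured, training status ignored | 0.701 | 0.098 |
| Half measured, training status ignored | 0.665 | 0.096 |
| Half measured, off-training indicator in the model | 0.632 | 0.100 |

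The last row is the useful one. Once the model knows who was off training, the overstatement disappears at a small cost in precision.

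**The case against.** A reader might infer that the plan hands every child who stops training the gains of those who continued, so that the result is always inflated. The documents do not support that, for three reasons.

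1. Item 11b plans post-intervention measures for children who drop out of the intervention. Item 20c imputes only what is missing, so it does not replace scores actually observed off training. If item 11b is carried out in full, the overstatement is zero.
2. Item 20c names no imputation model. Training dates, durations and frequencies are logged, and a model could use them. Such detail is commonly left to an analysis plan, which is not shown here, so its absence is not a fault in itself.
3. The only drop-out figure in the article is 10%. A larger bias, such as 0.70 against 0.56 at 20%, needs a drop-out rate that the documents do not give, as well as no quitter measured and no gain kept. Missing scores may also come from illness or relocation, and some exclusions are only temporary. A child who leaves midway may already have T3 or T4 scores that inform the imputation.

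There is also a fair objection to making the T1–T2 gain the sole primary basis for imputing quitters. Children are selected for low reading scores and the article itself recognises retest effects, so that gain may partly reflect regression to the mean and practice.

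What stands is narrower. Nearly the same non-training trigger leads to study exit in one section and to continued measurement in another. The single rule in item 20c is all that the article offers for the scores lost in between.

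**Conclusion.** The point holds conditionally. The article does not commit to a biased analysis. It leaves open a route by which unmeasured quitters are credited with trained children's gains, and the within-child design offers nothing to offset that.

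At the plan's own 0.70 and 10%, the overstatement lies between 0 and 0.07 in d. The upper end needs all three of the following: no quitter measured, no training gain kept, and an imputation model that ignores training status. It favours the intervention only to the extent that quitters gain less than children who continue, which is what the trial's main hypothesis would lead one to expect.

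In the simulation the largest bias is about three quarters of a standard error (0.07 / 0.094 = 0.74), and 0.63 is still about 6.7 standard errors from zero (0.63 / 0.094). At the planned drop-out, the size of the reported effect is therefore at stake rather than its detection.

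**What to change.** 1. Reconcile the exit criteria and item 18b with item 11b. The text should say whether outcome measurement continues after a child stops training or is excluded for not training, subject to consent. When a child should stop training is a separate matter and is not addressed here.
2. State that scores measured after training stops are used as observed.
3. For scores still missing after stopping, impute with a model that includes off-training status (exit date, logged training), informed by the measured quitters. At 10% of 120 that is about 12 children, so measured ones may be few. Where they are too few, use the T1–T2 gain under weekly therapy alone, and state the assumption that this gain represents ordinary progress.
4. Use standard imputation only for scores missing while the child was still training.
5. Report the imputation that treats all missing scores alike as a sensitivity analysis.

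The cost is a few sentences and some extra programming. Discharge dates are already on the identification form and training sessions are already logged on the software platforms. The downsides are slightly lower precision and, if some quitters go unmeasured, a somewhat smaller headline effect.

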### Plans to give access to the full protocol, participant level-data and statistical code {31c}

Additional data will be available online after recruitment completes.

### Composition of the data monitoring committee, its role and reporting structure {21a}

Monitoring of the clinical trial is guaranteed by the Laboratory of Anthropology and Clinical, Cognitive and Social Psychology (LAPCOS) and the Delegation for Clinical Research and Innovation of Nice University Hospital (DRCI) of the Nice University Hospital Center.

### Adverse event reporting and harms {22}

This trial intervention does not imply any adverse event or harms.

### Frequency and plans for auditing trial conduct {23}

The principal investigator is in constant communication with all the associate investigators in the online workgroup.

### Plans for communicating important protocol amendments to relevant parties (e.g. trial participants, ethical committees) {25}

The regional ethics committee (*Comité de Protection des Personnes Ile de France IV*) has approved the trial DDMR protocol (ID no. RCB 2019-A01453–54). The study has been registered in the ClinicalTrials.gov protocol registration system (NCT 04028310). Important protocol modifications will be submitted to the ethical committee CPP IDF VI for validation. Any modifications will be applied and added to the protocol. Modifications will be communicated in a new consent form to trial participants. The new protocol will be transmitted to investigators for application.

## Dissemination plans {31a}

Trial results will be communicated in publications.

## Trial status

Recruitment of participants started in September 2019 and will end in September 2021.

## Data Availability

This manuscript does not contain any data at this stage. The datasets generated and/or analyzed during the current study will be available in supplementary information files or through a permanent weblink to datasets.

## Abbreviations

DDMR: developmental dyslexia and method of remediation
ANOVA: analysis of variance
UCD: underlying cognitive deficits
SD: standard deviation
CP: categorical perception
PSM: phonological serial memory
RAN: rapid automatized naming
CRF: Case Report Form
DRCI: Delegation for Clinical Research and Innovation of Nice
